| We hypothesize that the use of a human coach-supported digital/AI personal health assistant (app) will improve adherence to cholesterol-lowering medications (statins with or without ezetimibe) among patients with hyperlipidaemia and suboptimal LDL-C control, when compared to standard care. |
| - 1. **Primary Objectives** |
| To evaluate the effectiveness of the human coach-supported digital/AI personal health assistant (intervention) on adherence to lipid-lowering medication at 6 and 12 months compared with those receiving standard care. |
| - 1. **Secondary Objectives**  1. To evaluate the impact of human coach-supported digital/AI personal health assistant on blood LDL-cholesterol levels at 6 and 12 months compared with those receiving standard care. 2. To evaluate the impact of human coach-supported digital/AI personal health assistant on atherosclerotic cardiovascular disease (ASCVD) risk at 6 and 12 months. 3. To evaluate the impact of human coach-supported digital/AI personal health assistant on health motivation and attitudes, self-care efficacy, self-care behaviours, and quality of life at 6 and 12 months. 4. To evaluate the acceptability of a new model of care 5. To evaluate the safety of a new model of care 6. To evaluate the (cost) effectiveness of human coach-supported digital/AI personal health assistant (intervention) on adherence to lipid-lowering medication at 12 months compared with those receiving standard care. |
| - 1. **Potential Risks and benefits:** |
| Potential Risks |
| There is minimal risk of loss of privacy breach associated with the use of mobile app. For example, if there is a data breach, someone who is not authorised could get information collected in the app. This chance is small, but it is not zero. There will be measures in place to minimum the risks in this study. |
| Potential Benefits |
| Patients in the intervention group will get full access the app and personalized Health Coaching sessions with a trained personnel to optimize management of their health condition for 12 months. |
| 1. **STUDY POPULATION** |
| List the number of patients to be enrolled. |

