| 1. Does not read or understand English. 2. Current use of smartphone medication adherence app(s) that include statins. 3. Concurrent use of PCSK9 Inhibitors in addition to statins and/or ezetimibe 4. Participation in another study that uses medications that could affect lipid levels 5. History of established atherosclerotic CVD, including but not limited to, atherosclerotic disease of coronary or carotid vessels or peripheral artery disease, documented ischaemic stroke (e.g., heart attack, cerebrovascular disease, peripheral artery disease) 6. Severe renal impairment defined as chronic kidney disease stage 4 and above. 7. Severe liver disease (Child-Pugh Class C) 8. Existing muscular-related complaints or diagnoses which may confound adverse event reporting 9. Uncorrected thyroid conditions, especially poorly-controlled hypothyroidism 10. Documented psychiatric diagnosis or history of mental illness or deemed as unable to give informed consent. 11. Currently pregnant, breastfeeding or expecting to get pregnant during the course of the study (1 year). 12. Guarded prognosis with expectant mortality within 12 months or less. |
| Withdrawal Criteria |
| Patients have the right to withdraw from (i.e., discontinue participation in) research at any time. They may be withdrawn from the study at the discretion of the investigator due if they fail to follow study procedure. |
| Patient Replacement |
| Patients who drop out may be replaced if the overall “lost to follow-up rate” is more than 20%. |
|  |
| **STUDY SCHEDULE** |

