| 1. **Clinical data:** Clinical data will be collected on a patient’s demographic details, past medical history, medication use, blood test results and anthropometric measurements. 2. **Questionnaires**: Onboarding questionnaire, DOSE Non-Adherence Measure and Psychometric Battery Questionnaires will be administered by the CRC 3. **Pill count**: Patients are required to bring along their prescribed lipid-lowering medications during their follow-up visits (@3m, 6m, and 12m). CRC will carry out pill counts with the patients during the visits. 4. **Medical care follow-up**: Standard-of-Care clinical pharmacist will follow-up with patients, titrating lipid-lowering medication (such as statin, ezetimibe etc) as required, and review and take action clinical blood test results (Appendix B; e.g lipid level, blood creatinine kinase and liver function tests where relevant). 5. **Human-AI-health coaching (For intervention only):** Health coach will use the information gathered by the AI chatbot to guide the targeted behavioural intervention during phone consultation. The scope of coaching will be strictly related to the medication adherence and general well-being. The coach will not start, stop, or titrate any medication. Coach will escalate concerns to clinical pharmacists when deemed fit. 6. **Focus group discussion (sub-study):** This will be conducted with a nested sample of 30-50 intervention group patients. The aims are: (a) to collect insights from intervention patients on their experiences with the app and human health coaching, (b) insights into which intervention components work best for them and under what circumstances, (c) insights into concerns which might impact intervention effectiveness, (d) factors that draw their participation and sustained engagement, (e) factors that deter them from sustainable engagement, (f) factors that may lead other CVD patients to be more inclined to partake in such a intervention and (g) ideas and suggestions to make the intervention more appealing and effective. |
|  |
| Randomisation and Blinding |

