| **Pre-screening, recruitment and Visit 1 (month 0)**  Primary care team will screen for non-adherence to statin using DOSE questionnaire, and if positive and primary care team will verbally explain the study to eligible patients. Should the patient be keen to participate in the study, the primary care provider will refer the patient to the CRC.  Upon recruitment and after randomisation, patients will be informed if they are allocated to be in the intervention or control group. Polyclinic CRCs will email a centralized team who are not involved in the screening and assessment of patients for the randomization outcome. Only the centralized team will have access to the randomization list that was pre-generated. The polyclinic CRCs will be blinded until the randomization outcome upon being informed.  CRC will administer the remaining questionnaires and take anthropometric measurements. Lastly, CRC will collect demographic and clinical information from electronic medical record.  **INTERVENTION:** Patients will be required to install the intervention app. The CRC will take the patient through the app features and answer any questions they may have.  Patients will receive curated, reliable and up-to-date medical information in an easily digestible and understandable format via in-app text message. The app can also send reminders via in-app text messages or push notifications to remind patients to take their medicine and their appointment dates. Our Artificial intelligence (AI)–based chatbots will prompt patients to engage in conversation to uncover their barriers to medication adherence and assist with setting personal goals.  **Follow-up Visits (Visit 2 @Month 3, Visit 3 @ Month 6 and Visit 4 @ Month 12**  The CRC will remind patients to bring their lipid-lowering medication before the study visits.  During the visit, the CRC will carry out pill counts, administer questionnaires and collect clinical information from electronic medical record. Anthropometric measurements will be taken at Visit 3 (month 6) only.  Clinical pharmacist will review clinical blood test results, monitor for safety and titrate lipid-lowering medications as required.  **Intervention Group:** Health coach will use the information gathered by the AI-based chatbot, such as patient's readiness to change, perceived barriers and misbeliefs to guide the targeted behavioural intervention via in-app text message or phone consultations. The scope of coaching will be strictly related to the medication adherence and general well-being. The coach will not start, stop, or titrate any medication.  **Focus group discussion (sub-study):** 30-50 Intervention patients who give consent for this substudy will be contacted by study team. The discussion will be held either in-person or virtually and will take approximately 3-4 hours. |

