| **Discontinuation Visit and Procedures** |
| In the case of patients withdrawing, or being terminated from the study due to unforeseen circumstances prior to the 1-year mark, they will be required to sign the Acknowledgment of Withdrawal form, and the CRC will have to acknowledge on the same form as well as confirmation. Patients’ decision to withdraw will not affect their medical care or any benefits to which they are entitled.  The CRC will access patient’s electronic medical record to collect clinical information (such as medications, blood test results, clinical events etc).  In cases where patient is uncontactable (“lost to follow-up”), every possible effort must be made to contact the patient and determine the reason for discontinuation or withdraws. Reasons for discontinuation or withdraws should be recorded, if possible. Clinical data collected prior to withdrawal will be retained for analysis, unless the patient disapproves it. |
| **TRIAL MATERIAL/DEVICE** N/A |
| **SAFETY MEASUREMENTS** |
| Definitions |
| **Adverse Event** – Any untoward or unfavourable medical occurrence in a patient or clinical investigation patient administered with a pharmaceutical product and which does not necessarily have a causal relationship with this treatment.  **UPIRTSO event** –refers to problems, in general, to include any incident, experience, or outcome (including adverse events) that meets **ALL** of the following criteria:   1. **Unexpected**   In terms of nature, severity or frequency of the problem as described in the study documentation (eg: Protocol, Consent documents etc).   1. **Related or possibly related to participation in the research**   Possibly related means there is a reasonable possibility that the problem may have been caused by the procedures involved in the research; and   1. **Risk of harm**   Suggests that the research places patients or others at a greater risk of harm (including physical, psychological, economic, or social harm) than was previously known or recognized.  **Serious Adverse Event** – A serious adverse event or reaction is any untoward medical occurrence which:   1. Results in or contributes to death; 2. Is life-threatening; 3. Requires inpatient hospitalisation or prolongation of existing hospitalisation; 4. Results in or contributes to persistent or significant disability or incapacity; or 5. Results in or contributes to a congenital anomaly or birth defect. |

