| The data collected will be screened for accuracy, missing data, outliers, and statistical assumptions. Following the principles of intention-to-treat (ITT) analysis, individuals will be retained in the group they were randomized to. At each measurement time, efforts will be made to minimize missing outcome data, and the reasons for individuals' loss of follow-up will be recorded. Missing data will be imputed using averages of answered items with no more than 20% missing data. When more than 20% of the items are missing, the overall score is not computed, and the data is considered missing. Sensitivity analyses will also be performed to determine the robustness of the assumption about missing data.  Descriptive statistics of baseline and follow-up data will be reported by mean and standard deviation for normally distributed variables, median and interquartile range for non-normally distributed variables, and proportions (count and percentage) for categorical variables. Continuous variables that are not normally distributed will be approximately normalised by using transformations and categorisations whenever applicable. Between group comparisons (by gender, age group, years since diagnosis, etc) will be made using Pearson χ2 or Fisher's exact test for categorical data, whereas continuous data will be tested with independent t-test and Mann–Whitney U test to evaluate changes between baseline and end-of-trial measures.  This study will also include regression/ modelling analyses to adjust potential confounders in this study such as gender, disease duration, number of comorbidities, and hypercholesterolemia treatment modalities (statins only, or ezetimibe, or statins plus ezetimibe). Subgroup analysis may be performed if the potential confounders found to be significant.  STATA (StataCorp Statistics for Windows, Version X, College Station, Texas) and R version X (The R Foundation for Statistical Computing; Vienna, Austria) will be used for all statistical analysis. All statistical tests will be performed using two-sided tests at the 0.05 significance level. |

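### The discontinuation procedure takes no adherence measure, so adherence after exit, including the 12-month primary value, is not collected for patients who leave early

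*Protocol*

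**What the plan says.** The primary objective (Protocol section 2) is the effect of the intervention "on adherence to lipid-lowering medication at 6 and 12 months compared with those receiving standard care". It names no instrument. The only adherence measures that the protocol names are the DOSE questionnaire and the pill count. Table 1 schedules DOSE at months 0, 3, 6 and 12 and pill counts at months 3, 6 and 12, in both arms, with no column for a discontinuation visit. Both need a contact with the coordinator. Section 6, item 3 says: "CRC will carry out pill counts with the patients during the visits". Section 6.3 says of the follow-up visits: "During the visit, the CRC will carry out pill counts, administer questionnaires and collect clinical information from electronic medical record".

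For patients who withdraw or are terminated before one year, the discontinuation part of section 6.3 says that "they will be required to sign the Acknowledgment of Withdrawal form". The coordinator then uses the "electronic medical record to collect clinical information (such as medications, blood test results, clinical events etc"). On earlier data it adds: "Clinical data collected prior to withdrawal will be retained for analysis, unless the patient disapproves it".

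Section 3.5 knows one kind of withdrawal: "Patients have the right to withdraw from (i.e., discontinue participation in) research at any time". Section 10.2 follows intention to treat, so that "individuals will be retained in the group they were randomized to". It also undertakes to keep missing outcome data low and foresees sensitivity analyses for the missing-data assumption.

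**The concern.** Record extraction can supply LDL-C, a secondary outcome, for a patient who has left. It does not supply the primary outcome as the protocol measures it. A medication list shows what was prescribed, and the protocol defines no adherence measure from it. So the plan keeps the secondary laboratory outcome for leavers and lets the primary one go, even where the patient is in contact to sign a form.

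Keeping patients in their randomised arm helps only if there is an outcome to analyse there. In an adherence trial, leaving may well be related to adherence. The trial is open-label, and only one arm has an app and coaching, so reasons for leaving may differ by arm. If both hold, the 12-month comparison among patients with data need not equal the comparison among all randomised. An analysis plan can choose how to treat missing values, but it cannot recover measurements that the protocol never asks for.

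**Working it through.** **Step 1: the procedures side by side.**

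| Contact | DOSE | Pill count | Electronic record |
|---|---|---|---|
| Visits at months 3, 6, 12 (Table 1, section 6.3) | yes | yes | yes |
| Discontinuation before one year (section 6.3) | not listed | not listed | yes |

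The open-ended list at discontinuation cannot fairly be stretched to cover DOSE or pill counts. Section 6 puts clinical data, questionnaires and pill counts under separate items, and the visit description in section 6.3 names record data as a third activity beside the other two. For the same reason it is unclear whether the sentence on retaining clinical data covers questionnaires and pill counts taken before withdrawal.

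**Step 2: whether another provision fills the gap.** The imputation rule in section 10.2 averages answered items within a questionnaire when up to 20% of items are missing. It does not address a visit that did not take place. Section 3.6 allows leavers to be replaced once loss exceeds 20%. That restores numbers, not the outcomes of the patients who left.

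**Step 3: the planned numbers.** Section 10.1 gives 376 patients (188 per arm) with at most 20% drop-out. The 376 itself can be neither confirmed nor refuted, because the metric of the effect size and the correlation between repeated measurements are not stated. The point does not rest on it.

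**Step 4: patients without a 12-month value at the ceiling.**

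- 376 × 0.20 = 75.2, about 75 patients without the value.
- 376 × 0.80 = 300.8, about 301 patients with it.

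**Step 5: leavers who still have a 6-month value.** The protocol gives no timing of withdrawals, so two patterns are assumed.

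- Constant hazard: 376 × √0.80 = 336.3 are present at month 6. About 40 have left by then, and 336.3 − 300.8 = 35.5 leave later.
- Linear loss: 376 × 0.90 = 338.4 are present at month 6. About 38 have left by then, and 338.4 − 300.8 = 37.6 leave later.

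Under either pattern roughly 35 to 38 of the 75 leavers, about half, can keep a 6-month value. The full range runs from none (all leave before month 6) to all 75 (all leave after it).

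**The case against.** A reader might infer more than the documents support, in four ways.

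- *That the primary outcome is lost for every early leaver.* The objective covers 6 and 12 months, and a patient who leaves after the month 6 visit has been measured at months 3 and 6. Only the 12-month value is missing for all of them.
- *That the comparison becomes one of completers.* Section 10.1 foresees the possible use of a mixed-effect model for repeated measurements, which can use earlier values from leavers, and section 10.2 promises sensitivity analyses. The details may stand in an analysis plan that is not at hand. What remains is that neither would have any adherence data after exit to draw on.
- *That a patient who tires of the app is handled as leaving the study.* No section says so. A patient who ignores the app and still attends is measured on schedule. What stands is that the protocol does not say that stopping the app or coaching leaves follow-up intact. The contents of the withdrawal form are not shown, and it may already offer that choice.
- *That the effect is overstated by 25%.* That figure is 1/0.80 = 1.25 (1/0.90 = 1.11 at 10% loss). It follows from assuming that every intervention-arm leaver gains nothing, otherwise resembles a control patient, and contributes no partial data. The protocol gives no basis for this. If less adherent patients leave both arms at similar rates, the bias could be small or go either way.

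It is also fair to say that the 75 includes patients lost to follow-up or refusing all contact, whom no wording will recover, and that a DOSE score on the day of exit is not a 12-month value. Both limit what the fix can achieve. Neither removes the gap.

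**Conclusion.** The point holds in limited form. As written, section 6.3 collects no adherence measure at or after discontinuation, so adherence after exit, including the 12-month primary value, is missing for early leavers. At the 20% ceiling this is up to about 75 of 376 patients. About half of them would keep a 6-month value if exits are spread over the year, which is an assumption. The count takes DOSE and pill count as the primary measures, because the protocol names no others. Bias in the 12-month comparison is possible if leaving depends on adherence and differs by arm; its size and direction cannot be derived from the protocol. This is a cheap improvement to a stated procedure and not a flaw that invalidates the design. It is best made before patients leave, because the data cannot be reliably recovered afterwards.

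**What to change.** 1. State in section 6.3 and on the withdrawal form that a patient may stop the app or coaching and still attend the outcome assessments at months 3, 6 and 12, with DOSE by phone if needed. Only full withdrawal from the study ends DOSE and pill-count collection. This is the main change, because it is the one that can supply the 12-month value.
2. As a fallback for patients who leave fully and agree, take DOSE at the discontinuation contact, and a pill count if the medicines are at hand. Label these as supportive data that do not replace the 12-month value.
3. State that questionnaire and pill-count data collected before withdrawal are retained on the same terms as clinical data.

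The change concerns data collection only and leaves clinical care as it is. It costs wording in the protocol and on the form, and a few minutes of coordinator time per leaver. It needs no extra staff or patients. Patients who refuse or cannot be reached remain missing.

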| **Table 1: Summary of Study Schedule**   \|  \| **Visit 1** \| **Visit 2** \| **Visit 3** \| **Visit 4** \| \| --- \| --- \| --- \| --- \| --- \| \|  \| **0m** \| **3m (± 2 weeks)** \| **6m (± 2 weeks)** \| **12m(± 2 weeks)** \| \| **Informed consent** \| **I, C** \|  \|  \|  \| \| **Collect demographic information from electronic medical record** \| **I, C** \|  \|  \|  \| \| **Download and install app** \| **I** \|  \|  \|  \| \| **Collect clinical data from electronic medical record** \| **I, C** \| **I, C** \| **I, C** \| **I, C** \| \| **Anthropometric measurements: Blood Pressure, height, weight, waist circumference** \| **I, C** \|  \| **I, C** \|  \| \| **Pill counts** \|  \| **I, C** \| **I, C** \| **I, C** \| \| **Questionnaires** \| \| \| \| \| \| - **Onboarding questionnaire** \| **I, C** \|  \|  \|  \| \| - **Dose Non-Adherence Measure** \| **I, C** \| **I, C** \| **I, C** \| **I, C** \| \| - **Psychometric Battery Questionnaires** \| **I, C** \| **I, C** \| **I, C** \| **I, C** \| \| **Clinical Pharmacist follow-up/review** \|  \| **I, C** \| **I, C** \| **I, C** \| \| **Human-AI-health coaching** \|  \| **I** \| **I** \| **I** \|   I = intervention, C = control |
| STUDY DESIGN |
| Summary of Study Design |
| This study is a multicentre, randomized controlled trial (RCT) on 376 hyperlipidaemia patients who are nonadherent to statins, with suboptimal LDL-C levels. These patients will be randomly assigned into one of the two groups: intervention group or standard care (control group) with a 1:1 allocation ratio. The intervention group will receive personalised feedback through the app coupled with human coaching on top of usual clinical care for cholesterol management. The control group will receive usual standard of care for lipid management but will not receive the personalised app nor have access to health coaching. |
| **METHODS AND ASSESSMENTS** |

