| Collecting, Recording and Reporting of “Unanticipated Problems Involving Risk to Patients or Others” – UPIRTSO events and “SAEs” to the NHG DSRB |
| The PI is responsible for the accurate documentation, investigation, follow-up and timely reporting of all UPIRTSOs and SAEs. Only related SAEs (definitely/ probably/ possibly) will be reported to DSRB. “Related” means there is a reasonable possibility that the event may have been caused by participation in the clinical trial  **Assessment of Events**  The PI must make a judgment about the **expectedness**, of an event. If the event is an adverse event, the PI must make a judgment about the **causality** of the adverse event. The PI must also analyse the event and state whether protocol / consent form revisions are required.  In the event of UPIRTSOs/Expected SAEs, the PI is responsible to ensure that adequate medical care is provided to the patient for treatment of adverse events.  **Reporting Timeline for UPIRTSO Events to the NHG DSRB.**  The PI must report all UPIRTSOs that occur during the conduct of a research project to the DSRB, in accordance with the timelines set by DSRB.   1. **Urgent Reporting:** All problems involving local deaths, whether related or not, should be reported immediately – within 24 hours after first knowledge by the PI. 2. **Expedited Reporting**: All other problems must be reported as soon as possible but not later than 7 calendar days after first knowledge by the PI. |
| Safety Monitoring Plan |

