| Safety and wellbeing will be assessed continuously in all patients participating in the study throughout the trial period. PI and co-investigators (co-Is) will provide day-to-day oversight of the trial. They will assure that informed consent is obtained prior to performing any research procedures, that all patients meet eligibility criteria and that the study is conducted according to the DSRB-approved research plan.  PI will evaluate the progress of the research study, including recruitment and retention, protocol deviations and an assessment of the timeliness and quality of the data on a biannual basis. They will also review the collected data including AEs and SAEs, unanticipated problems and withdrawal to determine if there is any change to the anticipated benefit-to-risk assessment of study participation. PI will ensure all protocol deviations, AEs and SAEs are reported according to the applicable regulatory requirements.  In addition to Serious Adverse Events that are unexpected or related, all Expected SAEs also should also be reported as soon as possible but not later than 7 calendar days after first knowledge by the investigator, and any additional relevant information about the events should be reported within 8 calendar days of making the initial report.  All research data will be stored within the institution. The completed questionnaires and informed consent forms will be kept in a locked cabinet in the respective recruitment sites. Only authorized study staff (PI, Co-I and CRCs) will have access to the research data. This is to ensure that all study information remains safe and secure. |
| Complaint Handling |
| Patients can contact the CRCs when they have complaints. The initial recipient of a complaint should communicate to PI without delay. The PI should acknowledge receipt as soon as possible, make every effort to resolve the issue after preliminary investigation. Any communication with the complainant should be documented. |
| **DATA ANALYSIS** |
| Data Quality Assurance |
| To ensure the accuracy and reliability of the data, PI, co-Is, CRCs, pharmacists, health coaches must be familiar with the protocol and all study-specific procedures. The app used has passed usability testing and load testing prior to being introduced to the study. This ensures that the data collected is uniform throughout all the patients in the intervention group. |
| Data Entry and Storage |

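### Safety is an objective, but no standard adverse-event question is set for the shared visits, and only the intervention arm has an extra route for side effects to surface

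*Protocol*

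**What the plan says.** Secondary objective 5 (section 2) is "To evaluate the safety of a new model of care". Section 8.3 adds that "Safety and wellbeing will be assessed continuously in all patients participating in the study throughout the trial period".

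Three parts of the protocol bear on how events would come to light.

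- **Shared by both arms.** Section 6.3, under the follow-up visits, says: "Clinical pharmacist will review clinical blood test results, monitor for safety and titrate lipid-lowering medications as required". Table 1 schedules "Clinical Pharmacist follow-up/review" for both arms at 3, 6 and 12 months, and "Collect clinical data from electronic medical record" for both arms at 0, 3, 6 and 12 months.
- **Intervention arm only.** The chatbot engages patients on what keeps them from taking their medicine, and the coach follows up by in-app text or phone (section 6.3). Section 6, item 5, adds: "Coach will escalate concerns to clinical pharmacists when deemed fit". Controls have neither app nor coach (section 5.1).
- **Recording and review.** Section 8.2 says: "The PI is responsible for the accurate documentation, investigation, follow-up and timely reporting of all UPIRTSOs and SAEs". Section 8.3 has the PI review AEs as well as SAEs twice a year. Exclusion criterion 8 removes patients with "Existing muscular-related complaints or diagnoses which may confound adverse event reporting", so the design itself treats adverse-event reporting as something to protect.

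**The concern.** Section 8.3 makes a promise for all patients, but no passage says how an adverse event is to be elicited. Table 1 has no adverse-event row. The CRC's follow-up tasks in section 6.3 are pill counts, questionnaires and record extraction. Sections 8.1 to 8.3 define events and set reporting duties without naming a question, a form or a recall period.

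Meanwhile the intervention is likely to bring side effects to light as part of its work. Section 1.1 lists side effects, real or perceived, among the reasons for non-adherence, and the chatbot is there to find such reasons. A symptom mentioned to it or to the coach can be passed to a pharmacist. A control patient with the same symptom has no matching study-initiated route. Patients and staff know the allocation.

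At stake is how objective 5 and the PI's biannual benefit-risk review are read. An excess of mild events in the intervention arm could reflect harm or better detection, and the data as collected might not separate the two.

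**Working it through.** The protocol states no adverse-event rate, safety margin or safety sample size, so there is no figure to reproduce. The check is mainly a comparison of the text by arm, followed by an illustration.

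**1. Routes by arm**

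| Route | Intervention | Control | Source |
|---|---|---|---|
| Pharmacist safety monitoring, months 3, 6, 12 | yes | yes | Table 1; 6.3 |
| Record extraction, months 0, 3, 6, 12 | yes | yes | Table 1 |
| Patient-initiated complaint to CRC | yes | yes | 8.4 |
| Standard adverse-event question by CRC | none named | none named | Table 1; 6.3 |
| Chatbot on barriers to adherence | yes | no | 6.3; 5.1 |
| Coach, with escalation to pharmacist | yes | no | 6, item 5; 5.1 |

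The last two rows are the asymmetry. That coaching takes place between visits is inferred from the text and phone mode, because Table 1 lists it under the visit columns.

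**2. Which events are exposed**

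Deaths, admissions and laboratory abnormalities can be found from records and pharmacist review in the same way in both arms. Non-serious events that are known only if the patient mentions them depend on who asks and how often.

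The shared sources are not fully insulated either. Coach escalations go to the pharmacists, and section 9.2 gives pharmacists and CRCs access to app data. An escalated symptom could then be written into the record and extracted from it. That last step is an inference.

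**3. Illustration of size**

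Let p be the true event rate, equal in both arms, and let c_I and c_C be the fractions captured. The observed risk ratio is

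(p × c_I) / (p × c_C) = c_I / c_C.

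It does not depend on p. With c_I = 1.00 and c_C = 0.80 it is 1.00 / 0.80 = 1.25. At p = 10% and 188 per arm (section 10.1), the expected counts are 188 × 0.10 = 18.8 against 188 × 0.08 = 15.0, with no true difference.

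The table gives the approximate chance that a two-sided 0.05 test (section 10.2) shows a significant excess in the intervention arm, with c_I = 1.00 and 188 per arm. The method is the normal approximation for two proportions. With equal capture the chance would be 2.5%.

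| c_C | Ratio | p = 5% | p = 10% | p = 20% | p = 30% |
|---|---|---|---|---|---|
| 0.90 | 1.11 | 4% | 5% | 7% | 9% |
| 0.80 | 1.25 | 7% | 10% | 17% | 26% |
| 0.70 | 1.43 | 11% | 18% | 34% | 52% |

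Both p and the capture fractions are assumptions. The ratio column only returns what was put in. The table shows when unequal capture would matter, not that it will occur to this degree.

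**The case against.** The strongest reply is that safety monitoring is scheduled, and equally so. The pharmacist review covers both arms at all three follow-up visits, and section 6, item 4, adds blood tests where relevant. Records are extracted on the same timetable in both arms, and either arm may take a complaint to the CRC. Objective 5 names no between-arm comparison, and how events are tabulated is commonly left to an analysis plan, which is not at hand. The contents of the psychometric battery are not shown either and might include a symptom item.

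Much of this stands, and it rules out several stronger readings that a reader might reach:

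- *That no safety enquiry is scheduled, or that controls are never asked about side effects.* The pharmacist's monitoring in both arms contradicts this.
- *That the arms' event rates cannot be compared, or that objective 5 cannot be answered.* Serious events, admissions and laboratory results are open to the same detection in both arms.
- *That non-serious events go uncollected because section 8.2 speaks of UPIRTSOs and SAEs.* That section concerns reporting to the review board, and section 8.3 refers to AEs among the collected data.
- *That the intervention arm will show an excess.* The protocol gives no capture rates, and at 90% control capture the effect is small.

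What the reply does not meet is narrower. The pharmacist's monitoring is part of standard care, with no stated question and no stated route into an adverse-event dataset. The complaint line is initiated by the patient and is not an enquiry about events. An analysis plan can choose which events to compare, but it cannot recover events that were never elicited.

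**Conclusion.** The point holds for non-serious, patient-reported events. Both arms share pharmacist monitoring and record extraction, but no standard adverse-event question is set for the shared visits, and one arm alone has an additional route for such events to surface in an open-label trial. A between-arm comparison of these events may be biased by unequal ascertainment, most plausibly towards more recorded events under the intervention.

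The size cannot be derived from the protocol. Under equal true rates the spurious ratio is the ratio of capture fractions: 1.11, 1.25 or 1.43 if controls capture 90%, 80% or 70% of what the intervention arm captures. Using all 188 per arm ignores dropouts. Fewer patients would lower the chances of a significant result but leave the ratio unchanged.

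The conclusion assumes that no questionnaire outside the document already asks a common adverse-event question. If one does, what remains is to record event source and define the comparison. The change should be made, because it is cheap and cannot be made after the visits have passed.

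**What to change.** 1. Add one row to Table 1: a single neutral, open question on any health problem since the last visit, asked by the CRC in identical words in both arms at months 3, 6 and 12, before coach or app notes are read. Do not prompt for muscle symptoms or any other named symptom. Section 1.1 makes the statin nocebo effect part of the rationale, and a named prompt could itself affect reporting and adherence.
2. Record the source of every event: visit question, pharmacist or record, coach or app.
3. Base any between-arm safety comparison on the visit question plus SAEs and hospital admissions taken from the record. List events that originate with the coach or app separately, so that they are still reviewed and reported but do not drive the comparison.
4. Reword the continuous-assessment sentence in section 8.3 to describe what is done and when.

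The cost is a few minutes at visits that already take place and one extra field on the case report form. Recorded event counts will rise in both arms. There is a small risk that asking at all prompts symptom reporting. The neutral wording limits it, and asking identically makes it equal across arms. No treatment or clinical rule changes.
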